### 2.14. Confidentiality

The personal information of the trial participants will be managed under the supervision of IRB. To ensure confidentiality, all the data collected from the trial will be treated anonymously. Third parties such as the monitoring committee for research purposes will only have access to de-identified data.

### 2.15. Dissemination Policy

The results of this clinical study will be presented at a congress and will be submitted for publication in relevant journals.

### 2.16. Trial Status

This is the latest protocol (version 1.1) approved by the IRB. This is an ongoing trial. The first participant was enrolled on 17 December 2021, and recruitment is expected to end in late 2023.

## 3. Discussion

In addition to acupuncture, which is covered by the NHI, pharmacopuncture is a common treatment modality for insomnia disorder in Korean medicine [31,32]. Pharmacopuncture is expected to have a combined beneficial effect in treating insomnia by physical stimulation through acupuncture and pharmacological treatment through herbal medicinal extracts [55]. A recent systematic review reported that pharmacopuncture can achieve significantly better sleep quality than pharmacotherapy or acupuncture [37]. However, due to methodological flaws and small sample sizes, it is difficult to draw concrete conclusions about the benefits of pharmacopuncture for insomnia and provide evidence for clinical decision-making. Another barrier to active pharmacopuncture implementation is the economic burden due to non-reimbursement of pharmacopuncture [36]. To reflect the clinical context of Korean medicine and provide evidence for clinical and policy decision-making, a pragmatic clinical study is required. Unlike traditional RCTs, which seek approval for a new drug or medical device, most Korean medical clinical studies seek to validate the efficacy of already clinically popular treatments or to compare their efficacy to that of alternative treatment strategies. As a result, pragmatic studies are appropriate for clinical trials in Korean medicine. Therefore, we designed a pragmatic RCT to compare the effectiveness of pharmacopuncture compared with acupuncture.

To the best of our knowledge, this study is the first pragmatic RCT to examine the effectiveness of pharmacopuncture in insomnia patients compared with acupuncture in south Korea. Furthermore, objective actigraphy data will be compared to subjective data from self-reported questionnaires to explore the consistency between objective and subjective sleep-related data. The findings should provide objective evidence of the effectiveness of pharmacopuncture and acupuncture for insomnia treatment. In addition, preliminary data on the effects of pharmacopuncture and acupuncture on sleep architecture and changes in sleep-related hormone levels will be provided.

In addition, we will be able to explore the influence of SES on sleep health of participants in this trial and identify the health disparities using the collected actigraphy data. We will also be able to investigate the effects of social and health inequality on the effectiveness of pharmacopuncture and acupuncture for insomnia. These findings might highlight that sleep health is an important component of public health and could provide evidence that pharmacopuncture can contribute to the public health by improving insomnia.

However, this study has some limitations. First, it is not possible to examine which type or acupoint in pharmacopuncture has the most significant effect on insomnia improvement, as we will allow for different types or methods of pharmacopuncture according to the practitioner’s clinical decision, depending on the patient’s condition. However, this policy can better reflect real-world Korean medical clinical practice, in which individualized treatment is performed. A retrospective analysis of medical records may provide complementary information regarding treatment details. We will detail the effects of these variations in the analysis and report the effectiveness of pharmacopuncture for insomnia. Second, we will only recruit patients with insomnia disorder; therefore, the generalizability of the results to insomnia patients with other comorbidities, including depression, anxiety disorders, alcohol dependence, and other disorders, might be limited. Third, the 4-week follow-up period in this trial is not sufficient to evaluate the persisting therapeutic effect of pharmcopuncture. Future studies with a follow-up period of 3 or 6 months are needed to investigate the long-term therapeutic effects of pharmcopuncture or acupuncture. Fourth, both participants and practitioners cannot be blinded to treatments because a sham acupuncture group could not be designed in this study. Therefore, we need to consider factors affecting treatment, such as participants’ expectations from pharmacopunture treatment, when interpreting the results of the study. Since the purpose of this trial is to investigate the effectiveness and safety of pharmacopuncture of uninsured treatment and acupuncture covered by NHI, this trial will not include a comparison between the intervention group and a third group treated with placebo or standard treatment as per Western medicine such as CBT-I. Further 3-arm trials including a placebo group to investigate the efficacy of pharmcopuncture compared to that of standard conventional treatment for insomnia. Finally, the insomnia-specific objective assessment tools will not be used as a primary outcome in this study. Although PSQI—the primary outcome variable in this trial—is not an insomnia-specific measurement, it allows convenient evaluation of sleep onset latency, total sleep time, and sleep efficiency, which are important parameters for assessing sleep improvement. In addition, we use ISI to examine the subjective perception of insomnia severity and actigraphy to objectively evaluate sleep. Thus, we expect to obtain subjective and objective data on the sleep improvement effects of pharmacopuncture and acupuncture.

## 4. Conclusions

Pharmacopuncture is expected to be effective in improving insomnia due to the combined effects of acupuncture and herbal medicine. The clinical evidence for the additional benefits of pharmacopuncture over acupuncture in insomnia treatment can promote further clinical research of various types and methods of pharmacopuncture. The results of this study are expected to provide evidence regarding pharmacopuncture for insomnia that will facilitate clinical decision-making and healthcare policy-making.

## Figures and Tables

**Figure 1 ijerph-19-16688-f001:**
[figure not shown]
Flow diagram of the study.

**Table 1 ijerph-19-16688-t001:** Schedule of enrollment, intervention, and assessment.

Time Point	Screening	Enrollment Allocation (V1) Treatment: Total 10 Sessions (V1–10)				Post-Treatment Evaluation	Follow-Up
	Week −1	Week 0	Weeks 1–4			Week 5	Week 9
		V1	V2–5	V6	V7–10	V11	V12
Eligibility screening	O						
Informed consent	O						
Vital signs	O	O	O	O	O	O	O
Socioeconomic status, medical history	O						
ISI, HADS	O						
Laboratory tests and electrocardiogram	O					O	
Randomized allocation		O					
Pharmacopuncture (experimental)		← 5 times per 2 weeks →					
Acupuncture (control)		← 5 times per 2 weeks →					
ISI	O	O		O		O	O
PSQI		O		O		O	O
PIT for insomnia		O				O	
CSEI-S		O				O	
VAS of subjective symptoms accompanying insomnia		O		O		O	O
Quality of life (EQ-5D-5L, EQ-VAS, SF-36, HINT-8), Cost data		O				O	O
Body composition		O				O	
Request for additional treatment						O	
Sleep diary and actigraphy	O	O	O	O	O	O	O
Adverse event check		O	O	O	O	O	O
PSG, melatonin, cortisol *		O				O	

* PSG will be performed a day before visits 1 and 10. Melatonin and cortisol levels will be collected at 10 p.m. a day before visits 1 and 10 and at 7 a.m. on visits 1 and 10. Only 15 participants per group enrolled at Pusan National University Korean Medicine Hospital. ISI, Insomnia Severity Index; HADS, the Hospital Anxiety and Depression Scale; PSQI, Pittsburgh Sleep Quality Index; PIT for insomnia, Pattern Identification Tool Insomnia for insomnia; CSEI-S, The Core Seven-Emotions Inventory Short Form; VAS, visual analog scale; EQ-5D-5L, 5-level EuroQoL five-dimension questionnaire; EQ-VAS, the EuroQol-visual analogue scale; SF-36, the 36-Item Short Form Health Survey questionnaire; HINT-8, Korean Health-Related Quality of Life Instrument with 8 items; PSG, polysomnography.

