### 2.2. Participants Recruitment and Study Schedule

A total of 138 participants with insomnia will be recruited and registered for competitive enrollment. Potential participants will be recruited through internal advertisements on bulletin boards and the homepages of each clinical institution, external advertisements in local newspapers, subway advertisements, and flyer advertisements. The investigators, who are qualified neuropsychiatrists of Korean medicine, will explain the purpose, treatments, procedures of the clinical trial, and any risks and potential for adverse effects that may occur during this trial procedure. Participants will be asked to sign informed consent forms after investigators sufficiently explain this clinical trial, and receive a copy of the consent form. The investigators will then diagnose the insomnia disorder according to DSM-5 criteria. Eligible participants will be randomly assigned to the pharmacopuncture or acupuncture group in a 2:1 ratio at visit 1. They will visit the research institution 12 times and undergo 10 treatments 5 times every 2 weeks for 4 weeks (visits 1–10). Within 1 week of treatment completion, a post-intervention assessment will be conducted (visit 11), and a follow-up assessment (visit 12) will be performed 4 weeks after treatment completion. The timeline of enrollment, treatment, and evaluation of the participants is summarized in Table 1, and a flowchart of the trial is presented in Figure 1. Additionally, 15 consecutive participants from each group enrolled at the Pusan National University Korean Medicine Hospital after random randomly assignment will undergo polysomnography, melatonin, and cortisol saliva studies on the day before the initiation of treatment (visit 1) and at the post-intervention evaluation (visit 11).

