#### 2.9.5. Additional Evaluation

To explore the effects of the interventions on sleep parameters, including sleep architecture and sleep-related hormones, 15 participants per group enrolled at Pusan National University Korean Medicine Hospital, where polysomnography referral is available, will undergo polysomnography and saliva study of melatonin and cortisol before the start and after termination of the treatment. We will assess sleep architecture (total sleep time, sleep efficiency, sleep latency, proportions [%] of non-rapid eye movement sleep [N1, N2, N3], rapid eye movement, and arousal index), respiratory events (apnea-hypopnea index, respiratory disturbance index, respiratory arousal index), periodic limb movement index, periodic limb arousal movement, and parasomnia events using polysomnography.

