### 2.13. Statistical Analysis

Continuous variables will be presented as means and standard deviations, while categorical variables will be presented as frequencies (%) and percentiles. The homogeneity of the demographic characteristics and baseline variables between the two groups will be evaluated to choose the appropriate analysis methods. The independent t-test or Mann–Whitney U-test will be used for analysis, depending on the normality of data distribution. If there were significant between-group differences in baseline variables or demographic characteristics, regression analysis with covariates (analysis of covariance) will be conducted. The primary and secondary outcome measures will be analyzed in the same manner. We will also examine the consistency between objective and subjective sleep-related data obtained from actigraphy and patient-reported questionnaires.

Additionally, we will analyze the changes in sleep parameters assessed using polysomnography and sleep-related hormones before and after treatment in participants who underwent polysomnography. Both the full analysis set (FAS) and per-protocol analyses will be conducted. The FAS is the primary analysis of effectiveness and safety. It will include all participants initially assigned to each group, except those who did not meet the eligibility criteria, those who had not received any intervention, or those who had not completed any outcome measurements. The per-protocol analysis will include participants who have completed more than seven sessions. All statistical analyses will be performed by an independent statistical expert blinded to the allocation and procedure using SPSS version 25 (IBM, Chicago, IL, USA). Statistical significance is set at *p* < 0.05.

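### The Table 1 footnote sets the second polysomnography and hormone measurement before the last treatment session; the text and the table row set it after treatment

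*Protocol article*

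**What the plan says.** The second PSG and hormone measurement is described in five places.

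- Section 2.2 schedules the two measurements "on the day before the initiation of treatment (visit 1) and at the post-intervention evaluation (visit 11".
- Section 2.9.5 says that the sub-study participants "will undergo polysomnography and saliva study of melatonin and cortisol before the start and after termination of the treatment".
- Section 2.13 announces the analysis: "we will analyze the changes in sleep parameters assessed using polysomnography and sleep-related hormones before and after treatment".
- In Table 1, the PSG, melatonin and cortisol row is marked under V1 and under V11, the post-treatment evaluation column.
- The footnote to that same row says "PSG will be performed a day before visits 1 and 10", and continues: "Melatonin and cortisol levels will be collected at 10 p.m. a day before visits 1 and 10 and at 7 a.m. on visits 1 and" (the visit number that closes this sentence is again the tenth).

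Two further statements in Section 2.2 fix what these visit numbers mean. Participants "undergo 10 treatments 5 times every 2 weeks for 4 weeks (visits 1–10", so visit 10 is the tenth session. The post-treatment visit comes after that: "Within 1 week of treatment completion, a post-intervention assessment will be conducted (visit 11".

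**The concern.** The footnote contradicts both the text and the row to which it is attached. It is also the only place that gives clock times, so it is the part that someone booking an overnight study and saliva collection would most naturally use. Followed as written, it yields a value obtained while treatment is still under way, which Section 2.13 would then analyse as a post-treatment value. If some bookings followed the footnote and others Section 2.2, the second measurement would mean different things for different participants, in groups of only 15. Every PSG and hormone endpoint in the sub-study rests on these same two measurements.

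**Working it through.** The protocol has no figure to reproduce here. The check sets the statements side by side and counts sessions.

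**Inputs.** Ten sessions, at visits 1 to 10 (Section 2.2 and the Table 1 header). Visit 11 within 1 week of completing treatment (Section 2.2). Fifteen sub-study participants per group at one site (Section 2.9.5). Total enrolment 138 (Section 2.2).

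**Sessions given by each candidate time point.**

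| Source | Second measurement | Scheduled sessions already past |
|---|---|---|
| Footnote, PSG | day before visit 10 | visits 1 to 9: at most 9 of 10 |
| Footnote, 10 p.m. saliva | day before visit 10 | at most 9 of 10 |
| Footnote, 7 a.m. saliva | morning of visit 10 | probably at most 9 of 10 |
| Section 2.2 and Table 1 row | visit 11 | all 10 |
| Section 2.9.5 | after treatment ends | all 10 |

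The count is an upper limit because a participant may have missed sessions. The 7 a.m. entry is only probable because the protocol does not say at what time of day the visit 10 session takes place. For the PSG and the 10 p.m. samples the order is certain: the day before visit 10 precedes the session at visit 10.

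**Distance between the two readings.** One treatment session, and in calendar time 1 day (to visit 10) plus up to 7 days (visit 10 to visit 11), so up to 8 days from the day before visit 10 to visit 11.

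**Participants potentially concerned.** 2 × 15 = 30, which is 30/138 = 22% of the planned enrolment.

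**Could this be a reading artefact?** That is unlikely. The footnote pairs visit 10 with visit 1 three times: for the PSG, for the evening samples and for the morning samples. The row's second mark sits in the same column as those for the pattern identification tool, the seven-emotions inventory and body composition, all of which are assessed post-intervention.

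**The case against.** The strongest reply is that the intended timing is plain. Sections 2.2, 2.9.5 and 2.13 and the table row all agree, and only the footnote differs, so the simplest explanation is a visit number written as 10 instead of 11. That may well be so, but the document cannot confirm it, and a slip in the only place with clock times still needs correcting.

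A second reply is that the site works from the IRB-approved protocol and its standard operating procedures, not from a footnote in an article. This stands in part: nothing shows that anyone was measured at the wrong time. A reader might infer that all 30 participants have mistimed data. The document does not support that; it holds only if the footnote was followed.

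A third reply concerns consequences. If everyone in both groups were measured on the night before visit 10, the data would still give a consistent contrast between baseline and late treatment, one session short of the full course. That also stands: such data would be mislabelled rather than worthless. Mixed timing would be the worse case.

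A reader might also infer that the discrepancy breaks a planned link between PSG and the PSQI, or takes PSG out of step with actigraphy. Neither is supported. Section 2.13 plans its objective-versus-subjective comparison for actigraphy and questionnaires, not for PSG, and Table 1 marks actigraphy in the V7–10 column as well as at V11.

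**Conclusion.** The contradiction is real and can be verified from the document alone. Under the footnote, the second PSG and evening saliva samples precede the last session with certainty, and the morning samples probably do. That is incompatible with "before the start and after termination of the treatment" in Section 2.9.5, with visit 11 in Section 2.2, and with the row's own mark.

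The size is modest: one session and up to 8 days, in a sub-study of 15 per group that the protocol itself treats as exploratory and preliminary. No bias in any PSG or hormone endpoint can be calculated from what the protocol gives. It would be wrong to read this as a threat to the main result: the primary PSQI comparison runs from visit 1 to visit 11 and does not use these data.

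The conclusion rests on one reading, namely that visit 10 carries the tenth session, which Section 2.2 and the Table 1 header both state. Whether any participant was actually measured early is unknown.

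**What to change.** Reconcile the footnote with Sections 2.2 and 2.9.5 and the Table 1 row, so that a single time point after the tenth session applies to every sub-study participant. Section 2.9.5 alone requires only that treatment has ended; Section 2.2 and the table row already specify visit 11, so adopting that introduces nothing new. The corrected footnote should express the night of the PSG and the two saliva clock times relative to that visit.

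The trial is described as ongoing. For participants already measured, record the actual date of the second measurement relative to their last session, and flag in the analysis any taken before it.

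The cost is a text correction, a note to the one site concerned and one date check per participant already measured. No additional procedure is needed.

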## Data Availability

The data presented in this study are available on request from the corresponding author.
